### Research objectives

The primary objective of the MOVING study is to examine the effects of an increase of PA and a reduction of ST after 6 months in the intervention group compared to the control group as assessed by accelerometry.

Secondary outcomes are whether there is an improvement of blood pressure, a reduction in weight and waist circumference as well as an increase of self-reported time doing PA, self-reported ST, and self-reported time doing PA as well as the effect of feedback letters on self-efficacy after 6 and 12 months.

Additionally, the impact of personal feedback letters on lifestyle (household, gardening, free time, and sport activities), quality of life and type of PA will be evaluated by questionnaire in the intervention group compared to control group after 6 and 12 months.

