### Random allocation

After screening and accelerometry, participants will be randomized 1:1 in the intervention and the control group. The randomization will be conducted using an automated function in the documentation software.

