### Power calculation

The sample size estimate was based on the amount of PA (mean time in min per day), measured in a comparable group of elderly people. In the study in question (Troiano et al.) the amount of PA was on average 15 min of combined PA (moderate and vigorous PA) per day [21]. We took these data as the starting point for the estimation of the required sample size. We assume that participants in the control group remain at approximately the same level while people in the intervention group increase their amount of PA by 20% [42], which corresponds to an increase from 15 to 18 min of PA per day after 6 months. To demonstrate this effect, a total number of 151 participants is needed (standard deviation 6.0 min, alpha = 0.05, power = 0.80). Assuming a loss to follow-up of about 30%, we will recruit 216 participants.

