### Data analysis

ActiLife software (version 6.13.2 or later, ActiGraph, Pensacola, FL, USA) will be used for data download and data processing. A valid measurement day is defined as a record of at least 10 h total wearing time and a record time of at least 4 days is required for data analysis. To categorize PA intensity, we used specific cut points based on Freedson [45]. PA is divided into sedentary (0–99 steps), light (100–1951 steps), moderate (1952–5724 steps), and vigorous (5725–9498 steps) PA. Step counts are based on 60-s epochs.

Statistical analysis will be conducted using pseudonymized data. First, the assessed project data will be descriptively analyzed. We will verify the conditions in both groups. In case of significant differences between the intervention and control group, analyses will be adapted accordingly and adjusted for relevant variables. Subsequently, the primary and secondary outcomes will be analyzed between the groups using *t* tests or corresponding non-parametric tests in case of ordinal variables or non-normality of the values. The tests will be conducted based on the intention-to-treat principle. The use of the intention-to-treat procedure ensures that each subject is included in the analysis. The analysis are carried out with the statistical software IBM SPSS Statistics (version 23.0.0.2 or later, IBM Corp., Armonk, NY, USA).

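### The plan says intention-to-treat brings every subject into the analysis, but its methods give no place to anyone without a valid 6-month recording

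*Protocol article*

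**What the plan says.** All of this is in the protocol article.

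- **Research objectives.** The primary comparison concerns physical activity and sitting time "after 6 months in the intervention group compared to the control group as assessed by accelerometry".
- **Data analysis, wear rule.** A day counts as valid only with 10 h or more of wear. The recording must also be long enough: "a record time of at least 4 days is required for data analysis".
- **Data analysis, tests.** Primary and secondary outcomes are compared between groups by t "tests or corresponding non-parametric tests in case of ordinal variables or non-normality of the values". Adjustment is foreseen only if the groups differ significantly.
- **Data analysis, analysis principle.** "The tests will be conducted based on the intention-to-treat principle". The next sentence adds: "The use of the intention-to-treat procedure ensures that each subject is included in the analysis".
- **Power calculation.** 151 participants are needed. "Assuming a loss to follow-up of about 30%, we will recruit 216 participants".

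The article names no imputation, no likelihood-based model and no other treatment of missing outcomes.

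**The concern.** Silence on missing data would be no finding in a condensed article. Here the article makes a positive claim: that the intention-to-treat procedure itself guarantees that everyone is analysed. The principle cannot do that. It says that participants are compared as randomised; a participant who did not return, or who wore the device too little, still has no 6-month value to put into a two-group test.

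The point matters in this trial because the outcome exists only if the participant comes back and wears the accelerometer long enough on enough days. Only the intervention arm receives letters built from that device, so return and wear could plausibly differ between arms, and could be related to how active people are. The target difference is small, 3 min/day. If the result is reported as intention-to-treat with every subject included, readers will not look for the attrition question that they ought to ask.

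**Working it through.** **1. Reproduce the plan's inflation.** Inputs from the Power calculation: 151 needed, about 30% lost.

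- 151 / (1 − 0.30) = 215.7, rounded up to 216. This matches the stated recruitment figure.
- Conversely, 216 × 0.70 = 151.2 remain and 216 × 0.30 = 64.8, about 65, are lost.

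The trial is thus sized so that about 151 supply the outcome, with the lost participants counted as contributing nothing. I take 151 as given; how it was derived has no bearing here.

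**2. Set the statements side by side.**

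| Statement | Consequence for a participant without a valid 6-month recording |
|---|---|
| Each subject is included (Data analysis) | Included |
| Minimum of 4 days' recording, valid day at least 10 h (Data analysis) | Not analysed |
| t or non-parametric test between groups (Data analysis) | Needs a value; none is supplied |
| 151 inflated for 30% loss (Power calculation) | Treated as not contributing |

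The first row cannot stand with the others unless a further method is added.

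**3. Invalid wear on top of loss.** The article does not say whether the 30% covers recordings that fail the wear rule. If it does not, and a fraction v of those followed up have invalid recordings (v assumed), the number analysed is 216 × 0.70 × (1 − v):

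- v = 0%: 151
- v = 10%: 136
- v = 20%: 121

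**4. Possible bias.** Let a fraction m of an arm be missing, and let the missing be D min/day less active than those observed in that arm. The full mean is (1 − m) × observed + m × (observed − D) = observed − m × D, so the observed mean is too high by m × D. With the same D in both arms, the available-case difference exceeds the all-randomised difference by (m_I − m_C) × D. All values of m by arm and of D are assumptions:

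| Missing, intervention v control | D (min/day) | Bias (min/day) | Share of 3-min target |
|---|---|---|---|
| 30% v 30% | any, equal in both arms | 0 | 0 |
| 35% v 25% | 3 | 0.10 × 3 = 0.3 | one tenth |
| 40% v 20% | 5 | 0.20 × 5 = 1.0 | one third |

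Each row averages the plan's 30% over two equal arms. If the loss were heavier in the control arm, the sign would reverse.

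**The case against.** The strongest reply is that the article states the aim, to include everyone, and leaves the mechanism to an analysis plan that is not shown. A t test can be run on imputed data, and inflating for dropout is ordinary planning that is compatible with a later imputation or mixed-model analysis.

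Part of this stands. A reader might infer that the plan prescribes a complete-case test on observed values. It does not say so. That reading is a well-supported inference, because no other method is named and the sample size counts on 151 remaining, but an unseen plan could specify imputation. The 30% is also not tied to the 6-month visit, so about 65 missing from the primary test is the natural reading and not a stated figure.

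The reply does not rescue the sentence itself. The article gives intention-to-treat as the reason why everyone is included, and that reason is wrong whatever the analysis plan adds. Any imputation would still have to be reconciled with the wear rule.

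A reader might also infer that people with an unusable baseline recording are randomised and then dropped. The article says only: "After screening and accelerometry, participants will be randomized 1:1 in the intervention and the control group". It does not say whether the recording is checked first. In a plain 6-month comparison an invalid baseline record would exclude nobody; it matters only if the outcome is change from baseline or is adjusted for baseline. The point does not depend on it.

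**Conclusion.** The assurance that each subject is included is incorrect on the methods stated and should be corrected before the analysis. As written, the primary test would in effect be an available-case comparison of about 151 of 216 participants. It would have fewer if invalid wear is additional to the 30% loss, for example 136 or 121 at an assumed 10% or 20%. It would be labelled intention-to-treat. This rests on taking the 30% as the loss at the primary time point and on the absence of any other method in the article.

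It would go too far to conclude that the trial's result will be biased, or biased by a third of its target. The documents give no loss by arm and no information on how active the missing participants are. The bias may be zero, and the 0.3 and 1.0 min/day figures only show how it scales under assumed inputs. What is established is a wrong assurance and an unprotected primary comparison, not a known distortion.

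**What to change.** 1. **Delete or correct the sentence.** State that participants are analysed in the arm to which they were randomised, and say how those without a valid 6-month recording enter the analysis.
2. **Change the primary analysis.** Use a linear mixed model for repeated measures on all randomised participants, with the accelerometer visits already scheduled (baseline, 3, 6 and 12 months), arm-by-visit terms, and the 6-month arm contrast as primary. Keep baseline as one of the repeated measures, so that a participant with only a baseline recording stays in the model. If minutes are skewed, as the plan's provision for non-parametric tests anticipates, use a transformation or robust or bootstrap inference. Multiple imputation followed by the planned comparison is an acceptable alternative.
3. **Add a sensitivity analysis.** Both methods assume that data are missing at random, which would not hold if dropout follows unrecorded motivation. A delta-adjusted or tipping-point analysis should show how far the missing would have to differ, by arm, to change the conclusion.
4. **Report as supportive** the available-case test and the numbers missing by arm, with loss to follow-up separated from invalid wear.

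The cost is a little more analysis work on data already due to be collected. A check of the baseline recording before randomisation, with a repeat wear week if it fails, is optional. It would change procedures during recruitment and is not needed to resolve this point.

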## Discussion

Previous studies have shown positive effects of interventions on PA and ST in older people using accelerometer devices. The interventions included using various different approaches, e.g., face-to-face consultations [24, 26] or regular telephone calls [46]. It seems to be difficult to transfer such complex procedures into routine practice due to the higher financial load and personnel expenses incurred.

On the basis of these considerations, our study was initiated to increase PA and reduce ST using a low-threshold intervention by providing automatically generated, individualized feedback letters containing health recommendations and personalized information about each participant’s PA and ST behavior. Over the course of the trial study participants twice receive individualized feedback based on accelerometer data. This method seems to be practicable to efficiently reach a high number of persons.

To promote PA in an adequate and lasting way, evidence on possible influencing factors is necessary. Therefore, the potential effect of self-efficacy on PA will be analyzed. Self-efficacy could be a relevant influence factor for changes in PA.

The results of the study will improve our understanding of PA and ST in older people and will provide evidence on how to increase the amount of PA and how to reduce ST behavior. If the intervention is effective, the study has the chance to reduce crucial risk factors for CVD and to improve quality of life, especially in the elderly.

### Trial status

The study started recruitment in November 2016, and is estimated to continue until the end of 2017. The final report will be prepared in 2018.

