**Methods/design:**

MOVING is a two-arm, randomized controlled trial. Inclusion criteria are age ≥ 65 years and the ability to be physically active. Exclusion criteria are the permanent use of a wheelchair and simultaneous participation in another study on PA.

At baseline participants who give informed consent will receive general information and recommendations about the positive effects of regular PA and less ST. Participants of both groups will receive an accelerometer device, which records PA and ST over a period of seven consecutive days following by a randomization. Participants in the intervention group will receive automatically generated, individualized feedback letters by mail based on their PA and ST at baseline and at 3-month follow-up. Further follow-up examinations will be carried out at 6 and 12 months.

The primary outcome is the increase of PA and the reduction of ST after 6 months in the intervention group compared to the control group.

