## Methods/design

The study region is Western Pomerania, a rural area in the Northeast of Germany.

MOVING (Motivation-Oriented interVention study for the elderly IN Greifswald) is a two-arm, randomized controlled trial consisting of participant screening, baseline examination, randomization, intervention, and follow-up examinations at 3, 6, and 12 months after baseline. The flow chart of the study is shown in Fig. 1.

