### Baseline examination

At the examination center, the participants are informed in detail about the study and invited to give written informed consent. Upon consent all receive a baseline examination consisting of blood pressure assessment and somatometry data (body weight, waist and hip circumference). All measurements are carried out by trained and certified study staff according to standard operating procedures (SOP).

In addition, all participants receive paper-pencil questionnaires to assess sociodemographics, general health, and actual PA behavior. To asses health status and quality of life the Short Form 8 (SF-8) questionnaire (German version) is used, which consists of eight scales addressing mental and physical health [31].

Furthermore, all study participants will receive the SSA scale (self-efficacy towards physical exercise) to assess each participant’s level of self-efficacy (twelve items which can be summed to a total score in which higher results indicate higher self-efficacy towards PA) [32]. To assess dietary habits, the Mediterranean Diet questionnaire (14 items, score ranging from 0 to 14) will be used [33]. Alcohol consumption will be assessed by using two items from the Alcohol Use Disorders Identification Test (AUDIT) [34].

After answering the questionnaires, all participants receive an accelerometer device (ActiGraph wGT3X-BT, Pensacola, FL, USA). The validated three-axis accelerometer device captures and records continuously PA and ST. Participants are instructed to wear the device during a period of seven consecutive days on the right hip and to remove it only for water-based activities (e.g., showering and swimming) as well as at bedtime. Data will be recorded at a sampling frequency of 30 Hz. Furthermore, participants are asked to document their activities in a semi-standardized daily protocol and to answer several paper-based questionnaires about PA and ST after the 7 days of accelerometer use at home.

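### The planned 6-month t tests use neither baseline activity nor season of entry; a pre-specified adjusted model would gain precision almost free

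*Protocol article*

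**What the plan says.** **Outcome and timing.** The abstract states "The primary outcome is the increase of PA and the reduction of ST after 6 months in the intervention group compared to the control group". The Methods/design section sets "follow-up examinations at 3, 6, and 12 months after baseline". Each visit yields one accelerometer recording: "Participants are instructed to wear the device during a period of seven consecutive days on the right hip" (Baseline examination, repeated under Follow-up).

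**Allocation.** Under Random allocation, "participants will be randomized 1:1 in the intervention and the control group". No stratification is mentioned.

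**Analysis.** Data analysis says that "the primary and secondary outcomes will be analyzed between the groups using" t tests, or non-parametric tests for ordinal or non-normal variables. Adjustment happens only after a significant difference between the arms, and the variables are not named. The section does not say whether the test is applied to the 6-month value or to the change from baseline.

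**Calendar.** Trial status: "The study started recruitment in November 2016, and is estimated to continue until the end of 2017", and "The final report will be prepared in 2018". Date and season appear nowhere in the sections on allocation, power or analysis.

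**The concern.** Two variables that may predict 6-month activity are available for every randomised participant with a usable baseline recording: the baseline accelerometer value and the date on which it was taken. A two-group t test uses neither. The adjustment clause does not fill the gap. It reacts to a significant imbalance and does nothing when the arms happen to be balanced, which is when a prognostic covariate still buys precision.

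The date matters because baseline and the primary visit are always half a year apart. If activity follows an annual cycle and entry is spread over the year, a winter entrant has a summer 6-month value and a summer entrant a winter one. That variation between participants is predictable but is treated as noise. On a change score the two seasonal deviations have opposite sign and add up. In a baseline-adjusted model without season they weaken the correlation between the two visits. At stake are power and interval width for moderate-to-vigorous activity (MVPA) and sitting time (ST).

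**Working it through.** **1. Inputs.** From Power calculation: 15 versus 18 min/day (difference 3), SD 6.0, alpha 0.05, power 0.80, 151 evaluable, 30% loss, 216 recruited. Assumed, because the article does not give them: two-sided alpha; correlation r between baseline and 6 months; seasonal amplitude a (half peak-to-trough) of 1, 2 or 3 min/day; SD 6.0 free of season; entry dates spread evenly over the year. No SD is given for ST, so only MVPA can be sized.

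**2. The plan's own figure.** Per arm, n = 2 × 6² × (1.960 + 0.842)² / 3² = 62.8, so 63 per arm and 126 in total (128 by the exact t test). The stated 151 does not follow from its inputs. The dropout step does: 151 / 0.70 = 215.7, so 216. The mismatch is a separate matter, and 151 (75.5 per arm) is taken as given here. Power at 151 is then 0.863 by the noncentral t (0.867 by the normal approximation).

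**3. Gain from the baseline term, no season.** Residual variance is 36(1 − r²), against 36 for the 6-month value alone.
- r = 0.5: 36 × 0.75 = 27.0, power 0.941.
- r = 0.6: 36 × 0.64 = 23.04, power 0.968.

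For comparison, a change score has variance 72(1 − r): 36.0 at r = 0.5 (power 0.863) and 28.8 at r = 0.6 (power 0.927).

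**4. Cost of leaving season out.** Let Y0 = μ + a·cos(t) + u + e0 and Y6 = μ − a·cos(t) + u + e6, where t is the entry date as an angle. The sign flips because the visits are half a year apart. With t uniform, cos(t) has variance 1/2, so:
- 6-month value: V = 36 + a²/2
- change: 72(1 − r) + 2a²
- baseline-adjusted, no season: V − C²/V, with C = 36r − a²/2
- baseline and season: 36(1 − r²)

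At r = 0.6 (variance; inflation against the same analysis free of season; power at 151):

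| a | 6-month value | Change | Baseline-adjusted | Baseline + season |
|---|---|---|---|---|
| 1 | 36.5; 1.01; 0.858 | 30.8; 1.07; 0.910 | 24.3; 1.05; 0.960 | 23.04; 0.968 |
| 2 | 38.0; 1.06; 0.844 | 36.8; 1.28; 0.855 | 27.9; 1.21; 0.934 | 23.04; 0.968 |
| 3 | 40.5; 1.125; 0.821 | 46.8; 1.625; 0.763 | 33.3; 1.44; 0.888 | 23.04; 0.968 |

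At r = 0.5, power on change is 0.844, 0.788 and 0.703 for a = 1, 2, 3, against 0.863 without season.

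**5. Which term does the work.** Adding baseline first and then season (r = 0.6), power moves 0.858 → 0.960 → 0.968 at a = 1, 0.844 → 0.934 → 0.968 at a = 2, and 0.821 → 0.888 → 0.968 at a = 3. Baseline dominates at the two lower amplitudes. At a = 3 the two steps are of similar size.

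**6. Dependence on the entry window.** For even entry over 14 months from November 2016, and an annual cycle peaking in mid-July, the season adds 0.491a² to a 6-month value and 1.963a² to a change score, close to a²/2 and 2a². The top inflation for 6-month values is then (36 + 0.491 × 9) / 36 = 1.12. For entry in November and December 2016 only, the additions shrink to 0.044a² and 0.176a². At a = 3 that is 0.4 and 1.6, or inflation of 36.4/36 = 1.01 and 30.4/28.8 = 1.06.

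**7. If SD 6.0 already contains season.** Adjusting 6-month values for season then raises power only from 0.867 to 0.869, 0.877 or 0.907 for a = 0.75, 1.5 or 3 (normal approximation).

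**The case against.** The strongest reply is that nothing here is an error. An unadjusted comparison under 1:1 randomisation is valid, and an article may leave the choice of covariates to a fuller plan. The first part stands. The second does not quite meet the point, because the article does commit itself: it names t tests and makes adjustment conditional on a significance test. A better rule can be set against that one.

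Three stronger readings are tempting, and the article does not support them.

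- *Opposite seasons at baseline and 6 months distort the result.* A shift shared by both arms cancels between them, and randomisation balances entry dates in expectation. Only the spread of entry dates adds variance, and entrants in April or October would show almost no swing if the peak is in mid-July.
- *The primary test is on change.* The abstract's wording ("The primary outcome is the increase of PA and the reduction of ST after 6 months") suggests it. But Power calculation compares 15 with 18 min/day using one SD and no correlation, which fits 6-month values at least as well. On that reading baseline season is irrelevant and the inflation is only 1.01 to 1.12.
- *The trial is underpowered because of season.* Power at 151 falls below the planned 0.80 only on a change score with a large assumed amplitude or a weak correlation.

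The amplitude, and indeed any seasonal effect, is not in the article. At a = 3 the peak-to-trough swing would be 6 min on a mean of 15, or 40%. The article also does not say whether SD 6.0 includes season.

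The entry window is open to dispute too, since the grammatical subject in Trial status is the study and not recruitment. If the whole study ended in 2017, 12-month follow-up would force entry into about two months and the seasonal loss would nearly vanish. Against that, the trial was registered on 17 May 2017 and the article still speaks of recruiting 216 participants in the future tense. Recruitment through 2017 is the more natural reading, but not a certain one.

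**Conclusion.** The point holds as a gain in precision that the plan leaves unused. It is not a bias and not a fault in the validity of the tests: the unadjusted intervals have correct coverage and are only wider than necessary.

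The firmer part is the baseline value. It needs no assumption about season, only a correlation. At an assumed 0.5 to 0.6, power at 151 evaluable goes from about 0.86 on 6-month values to about 0.94–0.97. The seasonal part is usually smaller and rests on an assumed amplitude, an SD free of season and entry spread over the year. A reader might infer that season threatens the primary conclusion; the article gives no figure that would show that. Minor to moderate, and close to free to correct.

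**What to change.** Replace the primary t tests for MVPA and ST with a linear model of the 6-month value on arm, baseline value and season of entry, the last as a sine and a cosine of the baseline wear date. State it in advance and drop the condition that the arms must first differ significantly. This also settles whether the analysis is of change or of the 6-month value. Because visits are at fixed intervals from baseline, the same season terms serve the 3- and 12-month visits. The unadjusted test can stay as a supporting analysis.

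The cost is a few lines in the analysis section and about 3 degrees of freedom (one for baseline, two for season). No new data are needed, since each baseline recording has a date. The change should be made before outcomes are compared by arm.
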